#### Effectiveness

Effectiveness will be assessed at pre- and post-treatment (3 months after first log in on the GET.ON platform or 6 months after the registration at IVPnet) with online surveys consisting of frequently used and well validated self-report questionnaires. Depressive symptoms are assessed using the German Version of the Patient Health Questionnaire 9 (PHQ-9) [87] with high values on internal consistency (α = 0.88) [88]. Generalised Anxiety Disorder severity is measured by the Generalised Anxiety Disorder 7 item self-report scale (GAD-7; α = 0.89) [89, 90]. Perceived stress is assessed with the German Version of Perceived Stress Scale with 4 items (PSS-4; α = 0.84) [91]. Somatisation tendencies will be measured by using the Somatic Symptom Scale based on 8 items (SSS-8; α = 0.81) [92, 93]. The 12-item Assessment of Quality of Life instrument (AQoL–4D; α = 0.81) [94] will be used to assess health-related quality of life. Subjective capacity to work will be assessed by using the Subjective Prognostic Employment Scale (SPE; Guttman scaling: rep = 0.99) based on 3 items [95]. Side effects attributed to the intervention are collected in the post-assessment period by the Inventory for the Assessment of Negative Effects of Psychotherapy (INEP; 22 items; α = 0.86) [96] adapted to internet- and tele-based interventions.

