#### Personalised tele-based coaching

The personalised tele-based coaching is provided by the company IVPNetworks (www.ivpnetworks.de) and focuses on general mental health problems. The coaches are psychologists with trainings either in cognitive behavioural therapy, systemic therapy, psychodynamic psychology, hypnotherapy or other therapeutic trainings. Licensed psychotherapists are responsible for supervision. The coaches support participants in recognising and understanding conflict patterns in order to effectively cope with issues by activating their own resources. This is pursued by approaching the participant’s personal situation and stressors (e.g., financial burden, family problems, work-related stress).

Participants are registered with their contact information in the IVPNetworks management and documentation platform (IVPnet 2.0). A case manager at IVPNetworks assigns the participant to a coach. The coaching is personalised in terms of amount, frequency and duration of the sessions, depending on the individual participant’s needs. Personalised coaching means that there are no standardised manuals or fixed procedures for the coaching. Different therapeutic methods are used depending on the therapeutic background of the coach (which will be monitored in the study). If indicated, participants are supported in finding on-site social and health care services to complement the tele-based coaching (e.g., socioeconomic consultants, agricultural family counselling). Alternatively, on-site coaching can be arranged if a participant no longer prefers tele-based coaching. Common content and duration of the personalised tele-based coaching at IVPNetworks are illustrated in Fig. 3.

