### Measurements

The used measures are summarised in Table 1, followed by a description of each RE-AIM dimension and selected outcomes. Measurements include routine data, staff reviews of intervention consultations as well as usage of the interventions by insured individuals, online-assessments, qualitative interviews and focus groups.

**Table 1 Tab1:** RE-AIM dimensions, measures and assessments

Dimension	Measure	Source	Assessment type	Time point
**REACH (individual level)**	Number and characteristics of potentially eligible insured individuals	SVLFG	Routine data	18 m
	Exclusion, referral und uptake rates; Completer rating from clinician’s judgement (Helping Alliance Questionnaire)	GET.ON Institute / IVPNetworks / SVLFG; GET.ON and IVP coaches	Reportings; Online-Assessment	Every 3 months; after participant is defined as (non-) completer
	Estimated number of people exposed to the recruitment, recruitment response rate in general as well as specific recruiting strategies	GET.ON Institute / IVPNetworks / SVLFG	Reportings	Every 3 months
	Representativeness of participants compared to eligible insured individuals and interested, but not participating insured persons	SVLFG	Routine data	18 m
**EFFECTIVENESS (individual level)**	Depressive symptoms (Patient Health Questionnaire 9), perceived stress (Perceived Stress Scale 4), generalised anxiety disorder (Generalised Anxiety Disorder 7 scale), somatisation (Somatic Symptom Scale 8), health-related quality of life (Assessment of Quality of Life 4D), subjective capacity to work (Subjective Prognostic Employment Scale)	Insured person	Online-assessment	T0-T2^a^
	Patient satisfaction (Client Satisfaction Questionnaire adapted for internet interventions), side effects (Assessment of Negative Effects of Psychotherapy)	Insured person	Online-assessment	T1^a^
**ADOPTION (organisational level)**	Number, proportion and characteristics of involved employees per organisation, characteristics of federal states and rollout areas, characteristics of insured persons and type of agricultural holding	GET.ON Institute / IVPNetworks / SVLFG	Sociodemographics of employees, routine data	R0^b^ Continuous
**IMPLEMEN-TATION (individual + organisational level)**	*Characteristics of the interventions:*			
	- Adaptations (TIDieR checklist)	GET.ON Institute / IVPNetworks	Reportings	Mid and end of the project

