	- Usage of the intervention (e.g. adherence, duration and frequency of contacts)	GET.ON Institute / IVPNetworks	Reportings	Continuous
	- Credibility (Credibility Expectancy Questionnaire) and perceived (dis-)advantages	SVLFG staff- participants	Online-assessment	R0 / R1 / R2 / R3^b^
	- Costs for the intervention	SVLFG	Reportings	Every 3 months
	*Outer Setting:*			
	Acceptance, relevance, utility	Insured person GET.ON Institute / IVPNetworks	Online-assessment Interviews Reportings (e.g. adherence)	T1^a^, T1^a^ Continuous
	*Inner Setting:*			
	- Leadership support (Implementation Leadership Scale)	SVLFG staff-participants	Online-assessment	R0 / R1^b^
	- Organisational willingness to change (Organisational Readiness for Implementing Change questionnaire)	SVLFG staff-participants, implementation team	Online-assessment	R0 / R1 / R2 / R3^b^
	*Characteristics of individuals:*			
	- Degree of normalisation (NoMAD)	SVLFG staff-participants	Online-assessment	R0 / R1 / R2 / R3^b^
	- Determinants of Behavioural Change (Discriminant Content Validation of the TDF Questionnaire)	SVLFG staff-participants)	Online-assessment	R1^b^
	- Barriers and facilitating factors at the consultations	SVLFG staff-participants	Focus groups	11/2017–02/2019
	*Process:*			
	- Evaluation of the implementation process (e.g. implementation activities, barriers and facilitating factors)	Implementation team	Interview	Every 6 months
	- Dissemination activities	SVLFG	Reportings	Every 3 months
	- Usage by employees	SVLFG staff-participants	Reportings	Every 3 months
	- Implementation costs	SVLFG	Reportings	Every 3 months
**MAINTENANCE (individual + organisatonal level)**	Sustainability of interventions (effectiveness)	Insured	Online-Assessment	T2^a^
	Referrals back to SVLFG and use of further offers	GET.ON Institute / IVPNetworks / SVLFG	Reportings	Continous
	Evaluation of the current implementation and further use of the technologies	SVLFG staff-participants	Online-assessment	R3^b^
	Sustainability of implementation (referral and uptake rates)	GET.ON Institute / IVPNetworks / SVLFG	Reportings	R3^b^

Notes

^a^time of insured-assessment depends on the date of intervention start

^b^time of employee-assessment depends on the date of the rollout in the specific area

*Abbreviation*: *m* month

Assessments: T0 (pre intervention), T1 (3 months after starting the internet-based training / 6 months after starting the tele-based intervention), T2 (12 months after starting the intervention)

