Intervention not started: The absolute number of referred persons who completed the assessment phase (IMIs: psycho-diagnostic assessment, tele-based coaching: first coaching assessment session) after the first contact with the external service provider, but have not started the intervention.In treatment: The absolute number of persons who have started the intervention after assessment phase (IMIs: first login into first module; tele-based coaching: receive tele-based coaching at minimum second session).Treatment not completed: Absolute number of persons who completed less than 50% vs. 70% of the intervention (IMIs: completed less than 50% vs. 70% maximal online modules within 13 weeks, have not logged in for at least 8 weeks or have interrupted the training for other reasons; tele-based coaching: completed less than 50% vs. 70% of the total call minutes, did not answer for at least 8 weeks or cancelled the coaching for other reasons).Treatment completed: a) In previous e-mental health studies, the completer criteria differed between 50 to 100% of completed units [81–84]. Research also indicates that a minimal treatment for subthreshold depression (e.g. six phone calls each with a maximum of 15 min) can also be effective in preventing MD [85]. Therefore, we defined two criteria with different treatment dosis as following: Absolute number of persons who completed at least 50% vs. 70% of online modules or call minutes. b) Clinical judgment by coaches at GET.ON Institute and IVPNetworks assessed with the Helping Alliance Questionnaire (HAQ) based on 11 items [86] in order to supplement the quantitative criteria for completion.Uptake of other services: This may include the crisis hotline, a second guided IMI, diagnostic clarification at IVPNetworks (via telephone or on-site), referrals to social or health service centres (e.g. socioeconomic or family consultants) during the tele-based coaching.

In addition, the estimated number of people exposed to recruitment materials and the associated response rate will be assessed. Specific recruiting strategies are tested to examine successful ways of addressing the target population. To provide representative information, interested but not participating individuals, and enrolled participants will be compared based on routine data. Differences in reach between the internet-, tele-based and on-site preventive services will be investigated as well.

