#### Maintenance

In assessing the maintenance of the implemented internet- and tele-based interventions, follow-up surveys with the insured participants will be conducted 12 months after first contact for the prevention project (e.g. 12 months after first login at the GET.ON platform or registration at IVPnet) to monitor the long-term impact of preventive interventions on mental health (see effectiveness measures, 60–65). Referrals to the SVLFG call centre are reported by the external service providers to capture all processes in the implementation that contribute to sustainable development. Uptake rates of the internet- and tele-based interventions are monitored in the maintenance phase of the respective rollout region. In terms of sustainability, we also record the use of a second IMI, the maintenance phase of the IMIs (e.g. monthly contacts for a year) or the prolongation of an IVP tele-based coaching and any other health care utilisation.

Normalisation is recorded in the maintenance phase using the questionnaire NoMAD [104] at the staff-level (e.g. field workers, in-house staff, call centre agents), and will be compared to the normalisation degree during the implementation phase. Additionally, the attitudes and experiences of the staff-participants involved in the implementation process are essential for sustained implementation. Therefore, a concluding survey with the staff-participants and important multipliers at SVLFG (e.g. management board) will be conducted at the end of the project to assess their professional view on the implementation and their intention to further use the internet- and tele-based prevention services. To ensure practical relevance, the item pool for this survey will go through an iterative feedback process with the initiators of the project.

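### Side effects attributed to the intervention are asked only at T1 (month 3 or 6), while the benefit scales run to month 12 and the plan allows use of the services after T1

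*Protocol article*

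**What the plan says.** **Side effects.** The Effectiveness section of the protocol article says: "Side effects attributed to the intervention are collected in the post-assessment period by the Inventory for the Assessment of Negative Effects of Psychotherapy". It gives the instrument 22 items and adapts it to internet- and tele-based delivery. In Table 1 (Measurements), the row holding "side effects (Assessment of Negative Effects of Psychotherapy" has T1 as its only time point.

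**Benefit.** The row directly above in Table 1 lists PHQ-9, PSS-4, GAD-7, SSS-8, AQoL-4D and SPE at T0 to T2.

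**Timing.** The notes to Table 1 define "T1 (3 months after starting the internet-based training / 6 months after starting the tele-based intervention), T2 (12 months after starting the intervention".

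**Use after T1.** The Maintenance section says that the study records whether a participant takes up another IMI, and likewise "the maintenance phase of the IMIs (e.g. monthly contacts for a year) or the prolongation of an IVP tele-based coaching". The section on tele-based coaching says: "The coaching is personalised in terms of amount, frequency and duration of the sessions", depending on individual need.

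**The 12-month survey.** Under Maintenance, "follow-up surveys with the insured participants will be conducted 12 months after first contact for the prevention project", with the purpose "to monitor the long-term impact of preventive interventions on mental health". The matching Table 1 row at T2 covers the sustainability of the interventions in terms of effectiveness. It does not list side effects.

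**The concern.** The plan follows benefit to month 12 and stops asking about attributed side effects at month 3 or 6. The Effectiveness section treats T1 as the post-treatment measurement, but for anyone who takes a second IMI, enters the IMI maintenance phase or has coaching prolonged beyond six months, treatment is not over at T1. These are the people with the longest exposure, and their later exposure has no side-effect question.

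At stake is the balance of the maintenance results. Long-term benefit would be reported without side-effect data for the same period. The schedule is fixed in Table 1, so this is not a detail left to an analysis plan, and no later analysis can recover answers that were never asked for.

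**Working it through.** The point concerns an assessment schedule. No power, alpha or event count is involved, and the plan gives no figure of its own to reproduce. The check sets the time points side by side and counts months.

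**Inputs**
- Last INEP (Table 1 and its notes): month 3 for IMIs, month 6 for coaching.
- Last participant survey (T2): month 12.
- IMI completion window (Reach section): "maximal online modules within 13 weeks", that is 13 × 7 = 91 days, or about 3 months.
- Data collection (Enrolment section): April 2019 to April 2021.

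**Time without a side-effect question = T2 − T1**

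| Service | Last INEP | Last benefit survey | Gap |
|---|---|---|---|
| IMI | month 3 | month 12 | 12 − 3 = 9 months |
| Tele-based coaching | month 6 | month 12 | 12 − 6 = 6 months |

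**What INEP at T2 would add for the IMI maintenance phase.** The article does not say when the year of monthly contacts begins, so both cases are shown as assumptions.
- Year starts at the end of training (about month 3): it ends at about month 3 + 12 = 15. T2 would cover months 3 to 12, which is 9 of 12 contact months (75%).
- Year is counted from first login: it ends at month 12, and T2 would cover all of it.

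For prolonged coaching no length is given, so no coverage share can be calculated. The 6-month gap follows from the schedule alone.

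**Who reaches T2.** April 2021 minus 12 months gives April 2020. Participants starting after about that date do not reach T2 within data collection. The T2 benefit scales share this limit.

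**Does anything else fill the gap?**
- The T2 scales can show worsening. The Quantitative analysis section compares pre, post and follow-up within groups, and participants choose their own intervention, so worsening cannot be assigned to the service.
- The Reach and Maintenance sections record service use such as the crisis hotline and other health care. These records do not ask about cause either.
- Table 1 places the participant interviews at T1.
- The Maintenance section refers to the effectiveness measures in general. That could be read to include INEP, which is described under Effectiveness, but Table 1 settles it by listing INEP at T1 only.

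**The case against.** The strongest reply is that this is a coherent choice. The text and Table 1 agree with each other. For IMIs, T1 coincides with the 13-week completion window, so side effects are asked at about the end of the core training. The study is an implementation study in which effectiveness is one of five dimensions. All of this stands: the plan contains no contradiction here, and T1 is a sensible time for a first side-effect assessment. It does not answer why the last assessment should also be T1 when use after T1 is provided for and the 12-month survey already takes place.

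Several stronger readings are tempting and are not supported:
- A reader might infer that the plan expects a year of contacts after T1. The Maintenance section only lists optional use to be recorded, gives the year as an example, and states neither how many continue nor when the year starts.
- A reader might turn the gap into a share of exposure covered. That would need the start of the contact year and the length of coaching, neither of which is stated in the text. It would also treat a monthly contact as equal to the module phase.
- A reader might conclude that no harm data are collected after T1. Symptom deterioration at T2 and further service use are recorded. What is missing is narrower: side effects that participants attribute to the intervention.
- A reader might suppose that the plan intends a claim of good tolerability. The Discussion speaks of acceptance, impact and long-term feasibility.

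**Conclusion.** The concern holds as an avoidable gap in the schedule. INEP at T1 only leaves attributed side effects unasked for 9 months (IMI) or 6 months (coaching) before the last survey, while the benefit scales cover that period. The two figures rest only on the definitions of T1 and T2. How much the gap matters depends on how many participants continue after T1 and for how long, which the article does not state. The remaining T2 data can show that some people worsened, but the uncontrolled design cannot say that the service was responsible. The change is worth making because the survey that could carry the question already exists.

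**What to change.** In Table 1, change the time point for side effects from T1 to T1 and T2, and bring the sentence in the Effectiveness section into line. Word the T2 form to ask about the period since T1. If questionnaire length is a concern, give it at least to those with further contacts after T1. Report T2 side effects by whether contacts continued (second IMI, IMI maintenance phase, prolonged coaching). The Maintenance section already provides for recording that use, so the grouping needs no new data.

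The cost is up to 22 more items in the existing T2 online survey, with no new visit or staff. Two limits remain. Participants starting after about April 2020 do not reach T2 before data collection ends. If the maintenance year starts at the end of training, its last 3 months or so would still fall after T2.

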#### Adoption

Adoption will be assessed through the number and characteristics of the involved employees at SVLFG as well as at the external provider (GET.ON institute, IVPNetworks). Furthermore, metrics of the rollout regions and federal states, such as amount and characteristics of insured people and type of agricultural holdings will be described and compared to one another.

#### Implementation

After a broad literature search, questionnaires were selected that fit the study context as best as possible (e.g. can also be used for employees who are involved in the referral and not in the service delivery itself).

##### Intervention characteristics

Potential adaptations to the existing interventions during the implementation process will be reported by the external service provider following the TIDieR checklist [51] halfway through the implementation and when concluding the project. Adaptations in the course of the implementation relate to referral and registration ways (e.g. to overcome barriers to participation). Furthermore, stakeholders’ (e.g. field workers, in-house staff, call centre agents) perception of perceived (dis-)advantages of internet- and tele-based interventions and the treatment credibility will be assessed using the Credibility Expectancy Questionnaire (CEQ) with 6 items [96]. The psychometric properties of the CEQ are characterized by high internal consistency (α = 0.84–0.85) and good values on test-retest reliability [97]. Intervention costs are recorded during the study as cost per participant for the respective intervention. Likewise, the use of the interventions by the insured individuals (including adherence, duration of intervention, number and duration of contacts, main topics, therapeutic background of coaches, etc.) will be monitored.

##### Outer setting

Constructs including participants’ needs and resources are related to the CFIR dimension ‘outer setting’ [43]. In assessing the outer setting, participant satisfaction is measured by using a German Version of the Client Satisfaction Questionnaire adapted for internet interventions (CSQ-I; α = 0.93) based on 8 items [65, 98]. The participants are asked about the usefulness and relevance of the interventions. Acceptance of the interventions is indirectly recorded via non-completer rates (indicator, see above). Approximately 20 semi-structured interviews each with participants from GET.ON chronic pain, from the six remaining IMIs and from the tele-based coaching will supplement the data collection and provide insights into the participants’ experience (e.g. acceptance, satisfaction, barriers and facilitators for intervention usage) with the internet- or tele-based interventions. The interview guide is based on the Unified Theory of Acceptance and Use of Technology (UTAUT) model [99] and the Discrepancy Theory of Satisfaction [100] with regards to the dimensions: technical quality of care, psychosocial quality of care, organisational conditions, spatial and technical equipment, treatment outcome, continuity of care and financing [100].

##### Inner setting

Constructs such as organisational culture and leadership engagement are related to the CFIR dimension ‘inner setting’ [43]. In assessing the inner setting, organisational readiness for implementing change for field workers, in-house staff, call centre agents and the implementation team at SVLFG is measured by using a German version of the Organisational Readiness for Implementing Change (ORIC) questionnaire with 12 items [101]. The ORIC questionnaire focuses on the degree to which employees are psychologically and behaviorally ready to implement organizational changes, which can be considered as a decisive factor for implementation success [101]. Good internal consistency (α = 0.88–0.92) is reported for the ORIC questionnaire [101]. Leadership of the implementation team as well as of the supervisors of field workers and call centre agents at SVLFG will be captured by using the Implementation Leadership Scale (ILS) based on 12 items [102]. The ILS can be seen as an efficient and short questionnaire which has been validated in settings of mental health with very high values on internal consistency (α = 0.93–0.97) [103].

